**14a. Maintenance of records, retention and storage of data**

Only the investigators named on the front of the participant information and consent document will have access to the research records, other than the participants.

Participants with PD will have access to their own data and to diary data only and on request. Participant carers will only have access to their diary data on request. There will be no cross-over of access by participants to any other data.

The research records will be stored in a secure place without reference to participant names. They will be coded to de-identify participants, and these codes will be used throughout the analysis of the results to ensure that the researchers are the only people who could match results with participant names. The data will be stored on an excel spreadsheet with a passcode to the data set, with a copy on an external hard drive. Only the CPI and CIs on this project will have access to the excel data sheet. Once the study is complete, all information that could be identifiable will be destroyed, and only the coded (de-identified) data will be kept for the period required by the HREC. The information and consent forms will be stored in a locked filing cabinet at Griffith University for 15 years.

**15. OUTCOMES AND SIGNIFICANCE**

The results of this study (will inform the researchers as to which dose and site of application, if any, influences outcome measures for people with Parkinson’s Disease. This information will provide the foundation dose methodology for a larger placebo-controlled trial for this patient population as well as information required to adequately power a larger trial.

**16. Anticipated Publication/Presentation**

De-identified results will be presented at conferences and in publications. It is anticipated that at least 4 publications can be produced from the data generated from the PD trials.

**17. CONTINGENCY PLAN**

In the event that the currently proposed protocol is unable to proceed due to uncontrollable and/or unforeseen restrictions or regulations (such as those imposed by government or global bodies e.g., COVID-19 pandemic lockdown restrictions) that directly or indirectly affect:

1. The study site(s).
2. The participant’s ability to participate in the currently proposed study protocol.
3. The researcher’s ability to conduct the currently proposed study protocol.

Several changes constituting a new contingency protocol will be formulated and implemented to adhere to such restrictions/regulations (See Appendix 8.). A layman’s version of the contingency protocol will also be included as part of the PICF and handed to participants as part of the recruitment and consent process, including a separate clause to indicate that participants have received, read, and understood the contingency protocol. Information about recruitment for the study will be advertised on public media platforms, with contact details available for interested potential participants to contact the research team directly.

**Appendix 1**

PDNeuro (LED) Primary Specifications:

- PDNeuro Helmet LED
- LED positions: Transcranial - 20 LED locations, each containing 1 x infra-red (IR) 810nm LED and 1x red 660nm LED; nasal – 1 x IR 810nm LED.
- Average power output: 660nm LEDs 71.2 mW; 810nm transcranial LEDs 103.4 mW; 810nm nasal LED 20mW.
- Duty cycle: 50% all diodes
- Treatment time: 660nm LEDs 12 minutes; 810nm transcranial LEDs 12 minutes; 810nm nasal LED 24 minutes.
- Total light energy delivered: 660nm LEDs 51.3 joules; 810nm transcranial LEDs 74.4 joules; 810nm nasal LED 28.8 joules; TOTAL = 154.5
- pulse frequency: all diodes 40Hz.

**Appendix 2**

**9-hole peg board test:**

Instructions and demo video for this can be found at:

<https://www.physio-pedia.com/Nine-Hole_Peg_Test>

**Step Test:**

Participants will place their foot up and back down on a standard height step (10cm) as many times as possible in 30 seconds. Both legs will be tested.

**TUG (timed up-and-go):**

Participants will be instructed to stand up from a chair, walk 3 meters (previously marked on the floor), turn around, return and sit down again. A standard chair 45 cm in height with arm supports at a height of 65 cm (using the floor as a reference) will be used. At the verbal command “Are you ready? Go” the participant will start the test. Time will be counted from the moment when the volunteer’s trunk no longer touches the back of the chair, to the point when the volunteer’s trunk returns to leaning against the back of the same chair. Time in seconds will be used for analysis. The TUG test will be performed three times: once normally, once carrying a cup of water (motor TUG) and once counting backwards in 2 from 100 (cognitive TUG). Instructions and video demo at:

<https://www.physio-pedia.com/Timed_Up_and_Go_Test_(TUG)>

**10m walk test:**

Participants will be instructed to walk at a pace closest to their habitual gait speed over a 10 meter distance, with time measured to travel the middle 8 meters to account for acceleration and deceleration. The variables of gait cycle that will be analyzed are: gait speed (m/s), cadence (steps/min), stride time (s), step length (cm), base of support (cm), single support (% of the gait cycle), and double support (% of the gait cycle).

Instructions and demo video at:

<https://www.physio-pedia.com/10_Metre_Walk_Test>

**Static and dynamic balance:**

The Mini Balance Evaluation Systems Test (Mini-BESTest) is a 14-item clinical test used to measure four components of balance control: anticipatory postural adjustments (sit to stand, rise to toes, stand on 1 leg), postural responses (stepping in four different directions), sensory orientation (stance – eyes open; foam surface – eyes closed; incline – eyes closed) and dynamic balance during gait (gait during change speed, head turns, pivot turns, obstacles; cognitive “get up and go” with dual task). Each item is scored from 0 (unable or requiring help) to 2 (normal), and the maximum score is 28 points.

**Spiral drawing test**

This is a pen-and-paper test. Publication embedded:

**Appendix 3**

**
[figure not shown]
**

**Appendix 4**

**Appendix 5**

**Appendix 6**

[figure not shown]

**Appendix 7**

[figure not shown]

**Appendix 8**

Contingency protocol

In the event that the currently proposed protocol is unable to proceed due to uncontrollable and/or unforeseen restrictions or regulations, the following changes will be implemented to the existing protocol constituting a new contingency protocol.

1. **Study design**
   1. Treatment will consist of home-based (in the participant’s own home) PBMt to the head and nose (either active or placebo treatment), 6 daily treatments per week for 12 weeks. Outcome measures to be supervised and data collected via the use of video link by Specialist Examiners and the Physiotherapists.
2. **Study setting/location**
3. Study location for both treatment outcome measures assessments will be changed to the participant’s own home.
4. **Inclusion criteria**
5. In addition to the inclusion criteria already stipulated, eligible participants will require:

   - Sufficient space (around 9 m^2^) to be able to perform motor assessments.
6. - Stable and sufficiently fast home-based internet connection for uninterrupted video calls and video conferencing.

   - Knowledge (self or carer) of using a phone and/or tablet applications on either IOS or Android platforms.**Study procedure**
7. In the absence of researcher/specialist-directed intervention, to ensure blinding of participants from group allocations and to reduce the change of participants inadvertently realising that they are in the sham, participants will be informed that there are 3 groups rather than 2 (Group 1: receiving red and infra-red light; Group 2: receiving infra-red light only; Group 3: receiving sham). In fact, there will remain to be 2 groups (Group 1: receiving red and infra-red light; Group 2: receiving sham).
8. **Outcome measures**
9. Outcome measures will be performed at the commencement of the trial before intervention (baseline, week-0), then after 2, 4, 6, 8, 10-weeks of treatment, and at the end of the trial (12-weeks of treatment), and at 6-months (3-months of zero intervention wash out).
10. All outcome measures will be conducted and recorded using a combination of self-reported assessment, visual assessment via video link with a specialist examiner (during live video or pre-recording by the participant).

1. **Consent process**
2. All previous in-person appointments during the consent process will now be conducted via video-link. For example:

   - Should a patient indicate an interest in participating in the study, the Principal Coordinating Investigator will contact the patient by phone or video link to answer any questions or to further explain the project and determine eligibility to participate in the project.

   - Patients and nominated carers will then be asked to re-read the Information Sheet and deliver the consent form electronically for live countersigning during their first video-link appointment.
3. **Additional screening, selection and other considerations**
4. In addition to the assessment of inclusion criteria and screening protocols being conducted via video telehealth communication, potential risk factors including falls risk, and cardiac comorbidities will be assessed live by qualified nominated geriatrician and cardiologist.
5. Additional exclusion criteria will include evidence of severe and unstable dysautonomia, recent cardiac surgeries (in the past 3-months), unstable arrhythmias (for a duration of 3-months), evidence of cardiac dysautonomia.
6. As an added duty of care, extra time will be taken to ensure that the overall speed and pace of any conversations between the research team and participant during screening and outcome measures assessments are suitable to account for the absence of in-clinic and personal supervision.
7. In addition to the original recruitment strategy, we will also employ public media platforms to present information regarding our study.

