**6. STUDY DESIGN**

Stage 2

Blinded, placebo/sham-controlled trial consisting of 40 participants. Group 1 (20 participants) will be

participants with Parkinson’s disease receiving treatment and Group 2 (20 participants) will be a placebo/sham-control group receiving no treatment. All groups will begin intervention in

August 2021. Treatment will consist of PBMt to the head and nose (either active or

placebo treatment), 3 times per week for 12 weeks. Outcome measures to be collected by Specialist

Examiners and the Physiotherapists.

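### Appendix 8's home-space rule of about 9 m² does not secure the 10 m walk test it is meant to allow, and the Mini-BESTest items are not adapted to video

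*Protocol*

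**What the plan says.** Section 17 provides for a contingency protocol if restrictions affect the sites, the participants or the researchers. Appendix 8 sets it out. Treatment and assessment move to the participant's home, and every outcome measure is obtained by self-report, live video or the participant's own recording. Among the added inclusion criteria is "Sufficient space (around 9 m^2^) to be able to perform motor assessments". It is an area; no length or shape is given.

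Appendix 2 defines the motor tests, and Appendix 8 changes none of them:

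- **10 m walk:** "Participants will be instructed to walk at a pace closest to their habitual gait speed over a 10 meter distance", with the middle 8 m timed and several gait-cycle variables derived.
- **Timed up-and-go (TUG):** "walk 3 meters (previously marked on the floor), turn around, return and sit down again", using "A standard chair 45 cm in height with arm supports at a height of 65 cm".
- **Balance:** the 14-item Mini-BESTest, scored out of 28, which includes "postural responses (stepping in four different directions" and "sensory orientation (stance – eyes open; foam surface – eyes closed; incline – eyes closed".

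The treatment schedule also differs. Section 6 has "3 times per week for 12 weeks", and the study procedure in Section 12 agrees. Appendix 8 has "6 daily treatments per week for 12 weeks". Assessments are at weeks 0, 4 and 12 and at 6 months in the main text; Appendix 8 adds weeks 2, 6, 8 and 10.

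Section 13b counts a participant as improved when the change between two time points exceeds half the baseline SD, and compares those counts between time points by chi-square.

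**The concern.** The space criterion exists so that the motor assessments can be done at home. A participant can meet it exactly and still have nowhere to walk 10 m in a straight line. The walk is a listed secondary outcome (Section 11), so under contingency it would either be missing for many eligible participants or be improvised differently in each home. An improvised course changes the measurement: the Appendix 2 version times only the middle 8 m so that acceleration and deceleration fall outside the timed part, and a course of about 4 m cannot do that over the same distance.

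The balance test has a similar gap. Foam and incline stance need equipment, and the stepping-response items are written for a clinic. Appendix 8 does not say which items are done remotely, or what becomes of the 28-point total if some are not.

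A further, conditional issue arises if some participants start in clinic and then move to Appendix 8. Treatment frequency, place and mode of assessment would change together, and a change from a clinic baseline to a home follow-up would carry all three.

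**Working it through.** **Plan's own figure.** The only derived figure bearing on this point is the energy per session in Appendix 1. Energy = power × time:

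- 660 nm: 0.0712 W × 720 s = 51.26 J
- 810 nm transcranial: 0.1034 W × 720 s = 74.45 J
- 810 nm nasal: 0.020 W × 1,440 s = 28.80 J
- Sum: 154.51 J, against 154.5 J stated. It reproduces.

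**Straight line available in 9 m².** Inputs: area 9 m² (Appendix 8); course 10 m (Appendix 2). The shape is not given, so two cases are shown.

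- Square: side √9 = 3.00 m; diagonal √(3² + 3²) = √18 = 4.24 m.
- Strip of length L: width = 9/L. For L = 10 m, width = 0.90 m.
- Reading *around* as 8 to 10 m²: the diagonal of a square is √(2 × 8) = 4.00 m to √(2 × 10) = 4.47 m, and the 10 m strip is 8/10 = 0.80 m to 10/10 = 1.00 m wide.

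The walk is therefore not ruled out by arithmetic, but it fits only a narrow corridor. In a square room it falls short by 10 − 4.24 = 5.76 m.

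**TUG.** Input: 3 m course plus chair and turning room (Appendix 2). Length left after the 3 m:

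| Space | Length used | Left for chair and turn |
|---|---|---|
| 3 × 3 m, along a wall | 3.00 m | 0 m |
| 3 × 3 m, diagonal | 4.24 m | 1.24 m |
| 4.0 × 2.25 m | 4.00 m | 1.00 m |
| 4.5 × 2.0 m | 4.50 m | 1.50 m |

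The TUG fits ordinary 9 m² shapes and is marginal only in a 3 × 3 m room.

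**What changes between the two protocols.**

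| | Main text | Appendix 8 |
|---|---|---|
| Planned sessions | 3 × 12 = 36 | 6 × 12 = 72 |
| Planned energy, active arm, at 154.5 J per session | 36 × 154.5 = 5,562 J | 72 × 154.5 = 11,124 J |
| Assessment times | 4 | 8 |
| Place | clinic | home |
| Mode | examiner present | video, self-recording or self-report |

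The energy row assumes that the Appendix 1 device settings also apply at home; Appendix 8 gives no others.

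**Part-way switch.** Section 17 lists restrictions on sites and on a participant's ability to take part as triggers, and a lay version of the contingency protocol is handed out at consent. A switch after some participants have started is therefore possible. The Section 13b rule would then set a follow-up taken at home against a baseline taken in clinic, and the shift in setting and regimen would enter the count of improved participants.

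**The case against.** Several stronger readings are tempting, and the documents do not support them.

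- **That contingency data cannot be pooled with clinic data, or that pooling them spoils Group 1.** The Protocol nowhere proposes pooling and calls Appendix 8 a new protocol. If the whole trial runs under it, both arms share schedule, place and mode of assessment.
- **That baseline is in clinic and follow-up at home.** Appendix 8 sets its own week-0 baseline, with its own screening and consent by video. Mixing arises only for someone who switches part-way. How such data are analysed is commonly left to a statistical analysis plan, which is not shown.
- **That 9 m² cannot hold the TUG, or that 4.24 m is the longest path the rule allows.** Both presume a square room. The criterion fixes an area only.
- **That three and six sessions a week contradict each other.** Appendix 8 introduces its content as changes to the existing protocol, so six is a declared change. What is missing is a reason for it.
- **That fall risk is ignored.** Appendix 8 adds live assessment of falls risk and cardiac comorbidity by a geriatrician and a cardiologist, together with further exclusions.

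Two further points limit the weight. Sections 11 and 12b list balance as static and tandem stance; only Appendix 2 describes the Mini-BESTest, so it is not certain that all 14 items were meant for home use. And the primary outcome is quality of life; questionnaires such as the PDQ-39 need no floor space.

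None of this meets the core point. The criterion is stated to serve the motor assessments, all measures are kept, and an ordinary room that satisfies it will not take the 10 m walk.

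**Conclusion.** The point holds in a narrow form. The area criterion in Appendix 8 does not secure the 10 m walk: 4.24 m at most in a 3 × 3 m room, or a strip about 0.9 m wide for the full 10 m. The appendix keeps the test without shortening or dropping it, and it leaves the foam, incline and stepping items of the Mini-BESTest unadapted to video or self-recording. The consequence is missing or non-comparable data on secondary gait and balance measures, and only if the contingency is used.

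This rests on taking *around 9 m²* at face value and on home spaces being room-shaped rather than corridors. The balance part also assumes that the Mini-BESTest as described in Appendix 2 is the test to be used at home.

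The risk to change scores is conditional on a part-way switch, which Section 17 permits but does not plan. A reader might infer that the contingency undermines the treatment comparison as a whole. It does not: if the whole trial runs under Appendix 8, the active-versus-sham comparison is not confounded by these changes.

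**What to change.** 1. In Appendix 8, do one of three things: replace the area with a required clear straight path length; specify a shortened home walk used at every visit including baseline; or state that the 10 m walk is not collected under contingency.
2. State which balance items are assessed remotely and how the reduced score is formed. Align Sections 11 and 12b with Appendix 2 on which balance test is meant.
3. For a part-way switch, add that half-SD change scores are not computed across settings, that a home baseline is needed for any home change score, and that clinic and contingency data are analysed as separate strata.
4. Reconcile the session frequency in Sections 6 and 12 with that in Appendix 8, or explain the difference. No view is taken here on which is right.

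The cost is a few sentences in the appendix and one stratum variable. With a path-length rule some homes will not qualify; with the third option one secondary measure is lost under contingency. Separate strata would make each analysis smaller than the planned 20 per group.

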**8b. Exclusion** **criteria**

Patients will be excluded from the study, if they:

- Are not capable of self-care
- Have a cognitive impairment with Montreal Cognitive Assessment (MOCA) score of <24
- History of significant psychotic episode(s) within the previous 12 months
- History of suicidal ideation or attempted suicide within previous 12 months.
- Take potentially photosensitizing medication, especially imipramine, hypericum, phenothiazine, lithium, chloroquine, hydrochlorothiazide, or tetracycline
- have a history of structural brain disease, active epilepsy, stroke or acute illness, factors affecting gait performance and stance such as severe joint disease, orthopaedic injuries, weakness, peripheral neuropathy with proprioceptive deficits, severe peripheral vascular occlusive disease, severe musculoskeletal disorders, uncorrected vision, vestibular problems or other severe conditions that would:
  - preclude the use of PBM therapy
  - place the patient at risk during evaluation of their PD, or
  - interfere with the evaluation of their PD
- have cardiac disease
- Patients who are currently participating in other trials regarding the treatment of PD, such as advanced therapies (Duodopa, Apomorphine, DBS).

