**Outcome** **measures**

Group 1 and 2: Outcome measures will be performed at the commencement of the trial before intervention (baseline, week-0), after 4 weeks of treatment, and at the end of the trial (12 weeks of treatment), and at 6-months (3-months of zero intervention wash out). In addition to the physiognomy measurements (weight, girth), motor coordination, balance, cognition, social cognition, smell test, carer diary and self-assessment outcome measures, participants will also be asked to provide faecal and saliva samples (for microbiome analysis) on 2 occasions; 3 samples before treatment begins and 3 samples at the end of the treatment period (12 weeks).

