**12b. Measurement tools used**

- Demographic data
- Physiognomic measurement (height and weight)
- Step test (Appendix 2)
- 10 meter walk test (Appendix 2)
- Spiral test (Appendix 2)
- Montreal Cognitive Assessment (MoCA) test (Appendix 3)
- Timed up-and-go (TUG) (Appendix 2)
- 9-hole peg board (Appendix 2)
- Static balance (feet apart, feet together, eyes open, eyes closed) (Appendix 2)
- Tandem balance (eyes open, eyes closed) (Appendix 2)
- Hand-writing assessment
- PDQ-39 questionnaire (Appendix 4)
- Parkinson’s disease sleep scale (PDSS) questionnaire (Appendix 5)
- Social cognition questionnaires (Appendix 6)
- Carer diary of daily activities (Appendix 7)
- Microbiome analysis (faecal and saliva sample)
- Heart rate variability
- Smell Identification test

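### Appendix 8 promises outcome tests supervised by video link but also allows the participant to pre-record them, and keeps no standing or gait test for live video

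*Protocol*

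**What the plan says.** Appendix 8 applies if restrictions prevent the main protocol from running. On location it states: "Study location for both treatment outcome measures assessments will be changed to the participant’s own home".

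Two paragraphs of the appendix then describe how testing is done:

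- Study design: "Outcome measures to be supervised and data collected via the use of video link by Specialist Examiners and the Physiotherapists".
- Outcome measures: "All outcome measures will be conducted and recorded using a combination of self-reported assessment" together with "visual assessment via video link with a specialist examiner (during live video or pre-recording by the participant").

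Appendix 8 removes no test from the main battery. Section 12b still lists "Tandem balance (eyes open, eyes closed) (Appendix 2"). Appendix 2 still describes the timed up-and-go (TUG) with a cup of water and while counting backwards. It also describes the Mini-BESTest, with one-leg stance, stepping responses, eyes-closed stance on foam and on an incline, pivot turns and obstacles. Section 8a admits patients up to age 85 and up to modified Hoehn & Yahr stage III.

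The protocol recognises the hazard. Section 8b excludes severe conditions that would "place the patient at risk during evaluation of their PD". For the home version, Appendix 8 adds that "potential risk factors including falls risk, and cardiac comorbidities will be assessed live by qualified nominated geriatrician and cardiologist".

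**The concern.** Live supervision and a recording made by the participant are different conditions. With a recording, the examiner sees the test after it is over and cannot stop it, correct it or repeat it. A site can therefore follow the Outcome measures paragraph of Appendix 8 to the letter and breach its Study design paragraph.

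Two things are at stake.

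- **Safety.** Balance and dual-task gait tests challenge stability on purpose. A fall during one would be an injury from a study procedure, in a trial whose primary hypothesis (section 5a) is that treatment has no adverse effects.
- **Measurement.** Section 13a makes baseline the reference point, and section 13b classes a participant as improved when the change between two time points exceeds half a baseline standard deviation. If baseline is tested live and a later visit is recorded, or the reverse, any effect of the mode enters that participant's change. If the mix differs between groups, it also enters their comparison.

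**Working it through.** The plan states no figure to reproduce here. The check compares passages and counts scheduled assessments.

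**1. Do the two paragraphs conflict?**

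| Feature | Appendix 8, Study design | Appendix 8, Outcome measures |
|---|---|---|
| Scope | Outcome measures, no exception | All outcome measures |
| Role of examiner | Supervises over video link | Assesses visually, live or from a recording |
| Tests kept for live video | Not addressed | None |
| Other person required to be present | Not addressed | Not addressed |

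The two can be reconciled only if pre-recording is confined to tasks that need no supervision. The text does not confine it.

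**2. Which tests does this reach?** It reaches every visually assessed test in section 12b and Appendix 2. Those done standing or walking are the step test, the 10 m walk, the three TUG runs, static and tandem balance, and the Mini-BESTest items.

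**3. How often?**

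- Main protocol (Outcome measures): baseline, then "after 4 weeks of treatment, and at the end of the trial (12 weeks of treatment), and at 6-months". That is weeks 0, 4 and 12 plus 6 months = 4 assessments.
- Appendix 8: weeks 0, 2, 4, 6, 8, 10 and 12 plus 6 months = 8 assessments.
- Ratio: 8 / 4 = 2.
- After baseline: 8 − 1 = 7 against 4 − 1 = 3.
- After baseline up to and including week 12: 6 against 2.
- TUG runs per participant, at three per assessment: 3 × 8 = 24 against 3 × 4 = 12.

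These are scheduled counts for a participant under the contingency from baseline who attends every visit. They are not counts of unsupervised tests, because the documents do not say what share would be recorded.

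**4. Do the stated safeguards cover a recorded test?**

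| Safeguard | Where | What it acts on |
|---|---|---|
| Exclusion for risk during evaluation | Section 8b | Entry |
| Live falls-risk and cardiac assessment | Appendix 8, Additional screening | Entry |
| Added dysautonomia and cardiac exclusions | Appendix 8, Additional screening | Entry |
| About 9 m² of space | Appendix 8, Inclusion criteria | Entry, setting |
| Suitable pace of conversation with the participant | Appendix 8, Additional screening | Live contact |

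The first four decide who enters and in what space. The fifth works only while someone is talking to the participant. None says how a pre-recorded test is to be done.

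**The case against.** The strongest reply is that the appendix should be read as a whole. The Study design paragraph sets the principle of supervision. The Outcome measures paragraph describes a combination of modes, and its word for all attaches to that combination, so it does not plan to pre-record every physical test. The pace-of-conversation item refers to contact during outcome assessments, which implies a live examiner. The contingency is also conditional, and the denser schedule is an open design choice, not an error. All of this is fair. It shows that supervised testing was probably intended, but the text still allows the other course.

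A reader might infer more than the documents support:

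- **That the falls assessment has no consequence.** The appendix adds to the main criteria and does not replace them, so the section 8b exclusion remains a route by which the assessment can act.
- **That carers have no part beyond app skills.** Nominated carers also take part in consent (section 14 and Appendix 8) and keep a diary (section 12b). The narrower statement is true: nobody's presence at a test is required.
- **That a fall would go unwitnessed.** A pre-recorded test is filmed, so a fall would normally be on the recording. What is missing is an examiner in real time.
- **That every motor test will be unsupervised.** The text permits this but does not require it.

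**Conclusion.** The point stands as an internal contradiction with a practical consequence. Appendix 8 promises supervision over video, then allows participant pre-recording without keeping any standing or gait test for the live session. Scheduled assessments double from 4 to 8, so the ambiguity applies to more occasions than in clinic.

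The conclusion assumes that pre-recording means the examiner views the test afterwards, which is the plain meaning of offering it as an alternative to live video. It also assumes that the main battery carries over unchanged, since Appendix 8 removes nothing. The documents give no fall rate and no estimate of the difference between live and recorded scores, so neither the added risk nor the measurement effect can be sized.

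The defect is confined to the contingency protocol and is easily corrected. It should still be corrected before that protocol is used, because it concerns participant safety and the consistency of the change scores.

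**What to change.** Amend the Outcome measures paragraph of Appendix 8 so that it agrees with the Study design paragraph:

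- Limit pre-recording to seated or paper tasks: spiral, handwriting, peg board and questionnaires.
- Do the TUG, 10 m walk, step and balance tests only in the live video session, with the examiner watching.
- Fix the mode for each measure and keep it the same at every visit. Record the mode with each result, so that any departure can be seen in the analysis.

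This takes one amended paragraph. The appendix already provides for examiners on live video and already requires an internet connection adequate for uninterrupted video calls. The cost is the scheduling of live sessions, and possibly some missed motor tests when a session cannot be arranged.
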